#### 2.3.2. Concealment and Blinding

Given the nature of the study, concealing allocated interventions to subjects or investigators is not feasible. The subjects will go through all interventions sequentially and will explicitly know what is expected of them in each intervention. Therefore, the subjects and investigators will not be blinded to the interventions’ allocation. However, the investigators will be blinded to the subjects’ allocation until the end of the baseline assessments as well as randomization assignments during the data analysis process (e.g., sleep analysis).

### 2.4. Run-In Period and Baseline Assessments

#### 2.4.1. Run-In Period Overview

The run-in period will take place one week before the launch of the experimental sessions in order to accomplish the following goals: (1) provide detailed information on the study flow to each participant; (2) stabilize the sleep window from 9:45 p.m. to 6:45 a.m. (compliance will be verified using accelerometers [Table S1]); (3) provide training for the participants on the use of the study’s measuring instruments (e.g., wearing the ambulatory polysomnographic device [PSG]); (4) complete baseline assessments; and (5) familiarize the participants to sleep with the PSG device.

#### 2.4.2. Baseline Assessments

Anthropometric and body composition: Body mass will be measured using a digital weight scale (UM-076, TANITA, Tokyo, Japan). Height will be assessed using a portable stadiometer with the participants barefooted (HR001, TANITA, Tokyo, Japan). The skinfold thickness will be measured in duplicate by the same investigator on the right side of the body at the biceps, triceps, subscapular, and supra-iliac sites using a Harpenden caliper (Baty International, Burgess Hill, UK). Relative fat mass will be then calculated using Siri equations amended by Weststrate and Deurenberg (1989) [26].The resting metabolic rate (RMR) and submaximal test: The resting metabolic rate will be measured in the morning, under a fasted state, by indirect calorimetry using a mobile spiroergometric system (METAMAX 3B-R2, CORTEX Biophysik GmbH, Leipzig, Germany). Before each test, the equipment will be calibrated according to the manufacturer’s recommendations. The participants will be placed in a supine position in a thermoneutral environment (22–25 °C room temperature) for 45 min before starting the measurements. After reaching a steady state, the O_2_ consumption and CO_2_ production, normalized for temperature, barometric pressure, and humidity, will be recorded and averaged at one-minute intervals for 20–45 min and averaged over the entire measurement period. The resting energy expenditure (in kcal/day) and the respiratory quotient (CO_2_/O_2_ ratio) will be calculated thereafter. The resting metabolic rate assessment will be followed by a submaximal test in order to estimate the peak oxygen consumption (VO_2_ peak) and therefore calibrate the energy deficit sessions’ exercise. The exercise will be performed on an adjustable cycle ergometer (Wattbike Ltd., Nottingham, UK). After a warm-up period (2 min), performed at 45 W, the output will be increased by 15 W every 5 min (allowing to ensure a stable state for each step) until the participants reach 60% of the age-predicted maximum heart rate amended by Tanaka et al. (2001) [27]. The heart rate (HR) will be continuously recorded using a heart rate sensor (Polar H10, Polar Electro, Kempele, Finland). The energy expenditure (EE) will be estimated for each step by multiplying the O_2_ consumption (VO_2_) by the energy equivalent (kcal/L O_2_) for each participant. The five steps will allow for the establishment of the HR–VO_2_ relationship for each participant, which will be used to calibrate the exercise intensity required for an expenditure of 125 and 250 kcal.Questionnaires: The to-be-completed questionnaires will include (1) the International Physical Activity Questionnaire (IPAQ) to estimate the physical activity level [28]; (2) the Morningness-Eveningness Questionnaire (MEQ) to determine the participants’ chronotype (i.e., evening, intermediate, or morning typology) [29]; (3) the Pittsburg Sleep Quality Index (PSQI) to assess the quality of sleep over the last month [30]; (4) the Dutch Eating Behavior Questionnaire (DEBQ) with scales for restrained, emotional and external eating behaviors [31]; and (5) the Multidimensional Fatigue Inventory (MFI) to assess fatigue traits [32].

### 2.5. Experimental Sessions

#### 2.5.1. Control Session

The control session (CTL) will be carried out over 28 h and starts when the participant wakes up (6:45 a.m.). Upon waking up, the participants will be equipped with accelerometers (GT3X+, ActiGraph LLC, Pensacola, FL, USA) on their waists until the next morning to monitor their physical activity. They will be asked to maintain their habitual overall level of physical activity, and any structured physical exercise during and 48 h before the session will be prohibited. Food intake will be organized over three scheduled meals (breakfast (7:15), lunch (12:30), and dinner (20:00)). The meals offered will be adapted to each participant’s preferences based on a panel of dishes proposed by the investigators (Table S2). The participants will be asked to take pictures of every consumed meal (habitual meal) and to fill out a food diary by weighing each consumed food item using a kitchen scale (EBC9i, EssentielB, Fretin, France) provided by the investigators. Appetite, sleepiness, and fatigue will be assessed throughout the day (i.e., 12 measures; Figure 2) using the Karolinska Sleepiness Scale (KSS) [33], Rating-of-Fatigue Scale (ROF) [34] and appetite visual analogue scale (VAS; 150 mm) [35], respectively. The Profile of Mood States questionnaire (POMS) [36] will be completed before bedtime. During the night, sleep will be measured by ambulatory polysomnography. The next morning, the participants will be asked to return to the laboratory in a fasting state. They will complete the Leeds Food Preference Questionnaire (LFPQ) [37,38] on a computer before being served a standardized ad libitum meal (buffet-style meal). After the meal, they will complete the LFPQ a second time. Sleepiness, fatigue, and appetite will be assessed throughout the morning (i.e., 8 measures; Figure 1). The control session will end at 10:35. 

The data collected during the control session will be used to assess the energy balance of each subject and to calibrate the food intake and exercises of the energy deficit sessions.

#### 2.5.2. Energy Deficit Sessions

All experimental sessions will be conducted similarly to the CTL session. As explained above, the sessions’ order will be randomized and counterbalanced. All meals will be taken at the same time, similar to the CTL session. All measurements will also be organized in the same way, and the participants will be asked to maintain the same level of physical activity as in the CTL session during the 3 experimental sessions, with no structured exercise during and 48 h before the start of each session. Physical activity will again be monitored by accelerometry. Thus, the only difference will be the energy deficit of 500 kcal, induced by the energy balance assessed during the CTL session. Energy deficits will be induced by 3 modalities corresponding to the 3 energy deficit sessions:DED session: 500 kcal dietary deficit (−250 kcal on breakfast and −250 kcal on lunch);EED session: 500 kcal deficit, induced by two exercise bouts (−250 kcal after breakfast and −250 kcal after lunch);MED session: 250 kcal dietary deficit (−125 kcal at breakfast and −125 kcal at lunch) and a 250 kcal deficit induced by exercise (−125 kcal after breakfast and −125 kcal after lunch).

During the DED and MED sessions, the food intakes will be replicated identically to the CTL session, while the portion sizes will be adapted to induce the desired energy deficit (i.e., the same standard food items with reduced amounts). During the EED and MED sessions, two exercise bouts will be performed on a cycle ergometer at the target HR corresponding to 75% VO_2peak_ at the same time (after breakfast and lunch, respectively). The only difference between the EED and MED sessions is a modification of the exercise intensity to induce the desired energy expenditure.

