#### 2.10.2. Statistical Analysis for Secondary Outcomes

The POMS questionnaire (taken before bedtime in each intervention) will be analyzed using repeated-measures ANOVA to assess the differences between interventions (followed by the Tukey HSD post hoc tests if necessary) and paired samples *t*-tests to evaluate the effect of each intervention separately against the baseline measures. 

The LFPQ will be administered twice, before and after an ad libitum meal on day 2. The paired samples *t*-tests will be computed for each intervention separately to assess the pre-post differences and the differences between the baseline and intervention measurements. A repeated-measures ANOVA will also be computed on the delta (post-pre LFPQ scores) to compare the score differences between interventions. Tukey’s HSD post hoc tests will be performed if significance is reached. Similarly, the food intake during the ad libitum meal will be analyzed using repeated-measures ANOVA (interventions comparisons) and the paired samples *t*-tests (the baseline-intervention comparisons). 

For the Karolinska, ROF, and hunger sensation scale, several measures throughout the day will be taken. In order to assess the time course of these measures for each day, the area under the curve (AUC) for each questionnaire will be calculated using the trapezoid method and analyzed using repeated-measures ANOVA for the differences between the interventions and using the paired samples *t*-tests for the baseline-intervention comparisons.

Manipulation checks will be performed (paired samples *t*-tests) on the energy balance measure between each energy deficit session to ensure that the induced energy deficit was isocaloric.

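### The manipulation check compares the deficit sessions only with each other, so it verifies neither the 500 kcal deficit nor a negative energy balance

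*Protocol article*

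**What the plan says.** Section 1.2 names the exposure as a moderate deficit of 500 kcal. Section 1.1 motivates it by asking whether exercise effects on sleep persist in negative energy balance, and section 3 interprets sleep in the same terms.

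CTL is the reference day (section 2.5.1). Dishes come from an investigator panel according to preference. Intake is self-recorded: "The participants will be asked to take pictures of every consumed meal (habitual meal) and to fill out a food diary". On activity: "They will be asked to maintain their habitual overall level of physical activity". The use of the day is stated as follows: "The data collected during the control session will be used to assess the energy balance of each subject", and the same sentence adds that it calibrates the deficit sessions. No target balance is given.

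Section 2.5.2 sums up how the deficit sessions depart from CTL: "Thus, the only difference will be the energy deficit of 500 kcal, induced by the energy balance assessed during the CTL session". The deficit sessions (section 2.5.2) then apply the same amounts to every man:
- DED: 250 kcal off breakfast and 250 kcal off lunch.
- EED: two exercise bouts of 250 kcal.
- MED: 125 kcal off each of the two meals, plus two bouts of 125 kcal.

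For DED and MED, "the food intakes will be replicated identically to the CTL session, while the portion sizes will be adapted to induce the desired energy deficit". EED food is covered only by the general statement that sessions run as CTL did.

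Section 2.6 calculates energy balance for each man in each experimental session, and section 2.1 counts CTL among those sessions. The only stated manipulation check is paired t-tests "on the energy balance measure between each energy deficit session", whose declared purpose is to show that the deficits were isocaloric (section 2.10.2).

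**The concern.** A manipulation check should show that the exposure in the objective was delivered. This one shows, at best, that the three modalities did not differ detectably from one another. CTL, the 500 kcal target and zero balance are all absent from it.

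Two statements are therefore left without planned support: that the men were 500 kcal below CTL, and that they were in negative energy balance. The second is how sections 1.1 and 3 use the term. If the men reduced their daily activity or misjudged portions to a similar extent in every session, the check would pass while the deficit was smaller than named. The declared purpose is also poorly served, because failing to find a difference in 24 men is weak evidence of equality.

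**Working it through.** **Plan's own figure.** The article's n = 24 (section 2.2.1) is the only sample-size input needed here, and it reproduces. For a repeated-measures ANOVA, λ = f²·N·m/(1 − ρ) = 0.25² × 24 × 4 / 0.5 = 12, with 3 and 69 degrees of freedom, which gives power 0.817. At N = 23 the power is 0.797. The point below does not depend on this calculation.

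**What the design delivers.** Let B be a man's balance on the CTL day and D the deficit actually delivered in a session relative to CTL. Session balance is B − D. By design D = 250 + 250 = 500 in DED and EED, and 4 × 125 = 500 in MED. With perfect delivery:

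| CTL balance (kcal) | Balance in each deficit session (kcal) | Difference between any two deficit sessions (kcal) |
|---|---|---|
| −500 | −1000 | 0 |
| −250 | −750 | 0 |
| 0 | −500 | 0 |
| +250 | −250 | 0 |
| +500 | 0 | 0 |

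The CTL values are illustrations; the article gives none. The last column is what the planned check sees, and it is the same in every row.

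**What the check can detect.** The difference between, say, DED and EED is (B − D_DED) − (B − D_EED) = D_EED − D_DED. B cancels. If every session falls short by the same amount s, the difference is (500 − s) − (500 − s) = 0, so s cancels too. With s = 200, for example, each session is only 300 kcal below CTL and the check still passes.

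**Non-significance as proof of isocaloric delivery.** The SD of a between-session difference in balance is not in the article, so a range is assumed. Power is for a two-sided paired t-test at 0.05 (noncentral t, 23 degrees of freedom, noncentrality (100/SD)·√24). The 95% CI half-width is t(0.975, 23)·SD/√24, with t = 2.069.

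| Assumed SD of difference (kcal) | Power to detect a 100 kcal gap | 95% CI half-width (kcal) |
|---|---|---|
| 200 | 0.65 | 84 |
| 300 | 0.35 | 127 |
| 400 | 0.22 | 169 |

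Across this range a true 100 kcal gap between two modalities would be missed in about 35% to 78% of trials.

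**Would the missing comparison be informative?** Yes. If the SD of session minus CTL were also 200 to 400 kcal, the interval would be 84 to 169 kcal either side of the mean. That is narrow enough to separate a 500 kcal deficit from none.

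**The case against.** The strongest reply is that nothing essential is missing. Balance is calculated in every session including CTL, so both comparisons can be made from planned data. The exposure in section 2.5.2 is already relative to CTL. A man's CTL balance is an offset shared by all his sessions, so it biases neither the comparison of modalities nor the session-versus-CTL contrasts in section 2.10.1. All of this stands. A reader might infer that the trial cannot show a deficit, or that its sleep contrasts are invalid; the article supports neither.

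A second reply is that the check was meant only to establish isocaloric delivery. That is its stated purpose, but it is the only check stated, and a non-significant t-test does not establish even that.

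A third is that calibration from CTL data, in section 2.5.1, might mean adjusting each man to an absolute 500 kcal below balance. The fixed amounts in section 2.5.2 make this the less natural reading. Table S2 is not shown, so menu energy may be specified there, and men on a specific diet are excluded (section 2.2.3). Neither safeguard is a stated target for the CTL day's balance.

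A reader might also want to state how many of the 24 men would not be in deficit at all. That number depends entirely on an assumed mean and SD of CTL balance, and the article gives no basis for either.

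**Conclusion.** The point holds as a defect in a stated check. The between-session t-tests return the same answer whatever the CTL balance was and whatever shortfall the three sessions share. They cannot verify the exposure in the main objective or the negative balance invoked in sections 1.1 and 3. That conclusion is algebra and needs no assumption beyond CTL balance not being set in the text. The power and CI figures rest on assumed SDs of 200 to 400 kcal and show only that non-significance is weak evidence.

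The consequence is for interpretation, not for the validity of the within-subject contrasts. By design the sessions are 500 kcal below CTL, not necessarily 500 kcal below energy balance.

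Two remedies that a reader might infer are not supported. Setting CTL menus to requirement before CTL would need expenditure data that the article does not place there: run-in accelerometry is described only for sleep-window compliance (section 2.4.1). Adjusting sleep efficiency for achieved balance would adjust for the exposure itself.

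**What to change.** Change section 2.10.2, using the balance already calculated under section 2.6:

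1. Report the mean and 95% CI of each deficit session minus CTL, set against −500 kcal.
2. Report the mean and 95% CI of each session's absolute balance, CTL included, set against zero.
3. Replace non-significance as the criterion for isocaloric delivery with the 95% CIs of the between-session differences, judged against a margin stated and justified in advance. An interval can lie inside the margin only if its half-width is smaller than the margin. If the SD were 300 kcal, no margin below about 127 kcal could be met with 24 men, so the team should be ready to report that isocaloric delivery was not demonstrated.
4. Describe the exposure as 500 kcal below the CTL day throughout, unless item 2 supports calling it a negative energy balance.

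The sessions, measurements and sample size stay as they are. The cost is one extra table and some wording.

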### 2.6. Assessement of Energy Balance 

The energy balance will be calculated individually for each participant during each experimental session. The EI will be calculated based on the computerized nutrient analysis software (Bilnut 4.0 SCDA, Nutrisoft) and the Ciqual tables (2020 version) based on the weight and food items recorded by the participants during Day 0 of each session. Energy expenditure (EE) will be calculated based on the RMR, daily metabolic equivalent of the task values derived from the accelerometer’s raw data for daily physical activity [39], and exercise energy expenditure (during EED and MED sessions).

### 2.7. Outcomes

#### 2.7.1. Primary Outcome: Sleep Efficiency

SE is defined as the ratio between total sleep time (TST) and total time spent in bed (TBT). It is given as a percentage. SE will be measured objectively during each session (i.e., CTL, DED, EED, MED) using an ambulatory polysomnograph (Sleep Profiler-PSG2, Advances Brain Monitoring, Carlsbad, CA, USA). The device is a portable multi-channel recorder that allows the acquisition of the following: the electroencephalographic (EEG), electrooculographic (EOG) and electromyographic (EMG) signals from three frontopolar channels; the airflow through a nasal cannula and pressure transducer; head movements and position by actigraphy; snoring, with an acoustic microphone; the pulse, using a forehead and finger sensor; the oximetry, using a wireless wrist oximeter; and the thorax and abdomen efforts by respiratory inductive plethysmography. The records will then be extracted through the Sleep Profiler portal. Validated auto-staging will be applied based on the ratios of the power spectral densities and the auto-detection of cortical and micro-arousals, sleep spindles, and ocular activity [40,41,42], which will be reviewed and modified by a sleep expert if needed. 

#### 2.7.2. Experimental Secondary Outcomes

Other sleep outcomes: Beyond SE, the Sleep Profiler-PSG2 provides other sleep variables, such as the following: total sleep time (TST); sleep onset latency (SOL); wake after sleep onset (WASO); the number of awakenings lasting more than 30 s; the arousal index and staging (time spent in non-rapid (NREM; Stage-1, Stage-2, and Stage-3) and rapid eye movement (REM)), according to the American Academy of Sleep Medicine recommendations [43].Mood: The Profile of Mood States will be used to assess the participant’s mood before the night of each experimental session [36]. All participants will be asked to rate “How are you feeling right now?” using 24 mood descriptors (e.g., nervous, unhappy, etc.). For each descriptor, the participants have to answer using a 5-point Likert scale, from 0 (not at all) to 4 (extremely). This questionnaire is divided into six subscales (fatigue, confusion, vigor, depression, tension, and anger), each containing four mood descriptors.Ad libitum energy intake: A standardized buffet breakfast will be organized on day1 of each session [44]. Consumed food items will be weighed and recorded by the investigators. Subsequently, the computerized nutrient analysis software (Bilnut 4.0 SCDA, Nutrisoft) and Ciqual tables (2020 version) will calculate the energy intake and the part of energy derived from each class of macronutrients.Food liking and wanting: LFPQ will be used to assess the individual’s food preferences [37]. It comprises two sub-tasks that require interactions from the participant. The first task (explicit task) involves an explicit assessment of food pictures using the 100-unit VAS. Single food images are randomly displayed to the participant on a screen computer, who is required to rate it according to “How pleasant would it be to taste some of this food now?” (explicit liking) and “How much do you want some of this food now?” (explicit wanting). The second task (implicit or forced choice task) requires a quick choice to be made between paired combinations of food pictures from different categories. During this task, a series of food image pairs are presented to the participant with the instruction, “Which food do you most want to eat now?”.Appetite sensations: Sensations of hunger, appetite, and a desire to eat will be measured using a VAS (150 mm) throughout all sessions (i.e., 9 measures on day 0, and 8 measures on day 1). These VASs were previously validated by Flint et al. (2000) [35].Sleepiness: The subjective level of sleepiness will be measured using the KSS [33]. The participant has to rate his subjective sensation of sleepiness in the last 10 min using a 9-point scale, ranging from 1 (extremely alert) to 9 (extremely sleepy).Fatigue: The French-validated version of the ROF scale will be used to assess the state of fatigue [34]. This is an 11-point scale, from 0 (not fatigued at all) to 10 (total fatigue and exhaustion), with accompanying descriptors and schematic components, which allow for tracking perceived fatigue across different ranges of daily life, physical activity, and recovery contexts.

#### 2.7.3. Baseline Secondary Outcomes

Subjective sleep quality: The PSQI questionnaire will be used to assess sleep quality [30]. It comprises 19 self-reported questions and measures seven components (i.e., overall sleep quality, sleep latency, sleep duration, sleep efficiency, sleep disturbances, use of medication for sleep, and daytime dysfunction due to sleepiness). The sum of scores from the seven components provides a global score from 0 (better) to 21 (worse). A global score of ≤5 is associated with good sleep quality; in reverse, a global score of ≥5 is associated with poor sleep quality.Eating behaviors: Eating behaviors will be measured using the DEBQ, a 33-item questionnaire assessing three distinct eating behaviors: emotional eating (13 items), external eating (10 items), and restrained eating (10 items) [31]. For each item, the participants have to answer using a 5-point Likert scale, from 1 (never) to 5 (very often), with higher scores indicating greater endorsement of the eating behavior.Chronotype: The MEQ will be used to define each participant’s chronotype [29]. The participants have to score 19 items using a 5-point Likert scale. The sum of the item scores ranges from 16 to 86. Scores of 41 and below indicate “evening types”, scores of 59 and above indicate “morning types”, and scores between 42–58 indicate “intermediate types”.Subjective physical activity. The short form (7 questions) of IPAQ will be used to assess the participant’s physical activity level [28]. The participants will be asked to report the time spent being physically active in the last 7 days using four different dimensions (i.e., vigorous physical activity, moderate physical activity, time to walk, and time spent sitting). Data collected with this questionnaire allow the classification of participants into three categories: inactive, minimally active, health-enhancing physical activity and/or to obtain a continuous measure reported as MET-minutes for each dimension (walking MET-min/week, moderate MET-min/week, and vigorous MET-min/week).Fatigue trait. The fatigue trait will be measured using the MFI questionnaire [32], which includes 20 items addressing different dimensions of fatigue, divided into 5 categories: general fatigue, physical fatigue, mental fatigue, reduced activities, and reduced motivation. The questionnaire includes positively and negatively worded items that are rated using a 5-point Likert scale. The dimension subscores (4–20) and global scores (20–100) can be calculated, with a high score indicating a high degree of fatigue.
